## Abstract

**Background:**

Understanding risks is considered to be crucial for informed decision-making. Inaccurate risk perception is a common finding in women with a family history of breast cancer attending genetic counseling. As yet, it is unclear how risks should best be communicated in clinical practice. This study protocol describes the design and methods of the BRISC (Breast cancer RISk Communication) study evaluating the effect of different formats of risk communication on the counsellee's risk perception, psychological well-being and decision-making regarding preventive options for breast cancer.

**Methods and design:**

The BRISC study is designed as a pre-post-test controlled group intervention trial with repeated measurements using questionnaires. The intervention-an additional risk consultation-consists of one of 5 conditions that differ in the way counsellee's breast cancer risk is communicated: 1) lifetime risk in numerical format (natural frequencies, i.e. X out of 100), 2) lifetime risk in both numerical format and graphical format (population figures), 3) lifetime risk and age-related risk in numerical format, 4) lifetime risk and age-related risk in both numerical format and graphical format, and 5) lifetime risk in percentages. Condition 6 is the control condition in which no intervention is given (usual care). Participants are unaffected women with a family history of breast cancer attending one of three participating clinical genetic centres in the Netherlands.

**Discussion:**

The BRISC study allows for an evaluation of the effects of different formats of communicating breast cancer risks to counsellees. The results can be used to optimize risk communication in order to improve informed decision-making among women with a family history of breast cancer. They may also be useful for risk communication in other health-related services.

**Trial registration:**

Current Controlled Trials ISRCTN14566836.

## Background

Risk communication aims to improve people's understanding of health risks in order to contribute to informed decision-making. Of particular interest and complexity are risks regarding hereditary or familial cancer, such as breast/ovarian or colon cancer [1]. It is commonly assumed that 5–10% of all breast cancer cases can be attributed to a genetic predisposition, of which the breast cancer genes *BRCA1 *and *BRCA2 *have been identified as most important [2]. Mutations in these genes increase the lifetime risk of breast cancer substantially, e.g. from a 10% population risk [3] to a risk of 60–85% of developing cancer by age 70 [4,5]. However, *BRCA1/2 *mutations account for only a small subgroup of women with a family history of breast cancer. A substantial group of women attending genetic counselling because of their family history have a slightly (11–20%) or moderately (20–30%) increased risk of getting breast cancer. Genetic counselling generally takes place at specialised centres and focuses on the communication of personalised risk information. The aim is to have a well-informed counsellee, who understands both risks and consequences, and acts accordingly [6].

The multiple risks and uncertainty of the risks, e.g. because of the incomplete penetrance of *BRCA1/2 *mutations, introduces complexity into risk communication regarding hereditary and familial breast cancer. Based on these complex risk contexts, decisions have to be made such as whether and when to start mammography screening, and, assuming eligibility, whether to test for mutations in *BRCA1/2*, and subsequent decisions in the case of positive or negative genetic test-outcome. Understanding risks is considered to be crucial for informed decision-making [7], whereas inappropriately high (or low) perceptions of risk can lead to various and potentially harmful decisions, for example overscreening due to overestimation of risk [8]. Overestimation of risk is also shown to be positively correlated with breast cancer worry, which may affect psychological well-being negatively [9]. Previous studies found a high percentage of unaffected women with a family history of breast cancer overestimating their breast cancer risk, although underestimating also occurred (see review [10]). In general, genetic counselling decreases generalized anxiety [11], and significantly improves the accuracy of women's perceptions of their breast cancer risk [11,12], but not necessarily to the correct level [11], or for the long term [12]. Therefore, it is important to identify strategies that will optimize understanding of risk.

Risk communication in genetic counselling is difficult, not only due to the complexity of the risks involved, but also due to problems that counsellors themselves experience in conveying these risks in an understandable way [13]. In addition, the counsellee's understanding and retention of the information given may be problematic. Personal experiences with breast cancer and counsellee's personal characteristics could have mediating effects on the efficacy of risk communication. For instance, the impact of a woman's family history can influence her risk perception prior to counselling through phenomena such as "anchoring" or availability heuristics [14]. Additionally, people with a high need for cognition potentially process risk information more thoroughly and have a higher need for additional risk information compared with people with a low need for cognition [15]. Moreover, women who face difficult decisions with respect to, for instance, genetic testing, may cope differently as a result of their dispositional decision-coping patterns [16].

Regarding the risk communication process, research has shown that the context and format in which genetic risks are presented affect people's risk perception, and their subsequent decisions [17,18]. Although risk presented in numeric terms are precise and preferred by healthy counsellees [19] and patients [20], risks in verbal terms (e.g. "a high risk") are generally more familiar and easier to understand. However, the inherent vagueness of verbal risks leads to substantial variation in their interpretation [21,22]. Risks presented frequentistically (e.g. "1 in 10 cases"), may result in more accurate risk perception and better-founded decisions compared with risks presented in percentages [23]. When frequencies are used, rates (i.e. X in 100) are easier to understand than proportions (i.e. 1 in X) when comparing risks [24]. In sum, both numerical and verbal formats have their pros and cons (see also Lipkus [25]). Several recommendations have been made directed at the use of graphical displays in risk communication [25,26], which may provide helpful support, particularly for persons with low cognitive capacity such as low levels of numeracy [26,27]. Baty et al., for example, reported that graphical displays enabled women to quickly understand their risks of getting breast cancer [28]. However, others have shown that risks presented as icons or pictographs (e.g. population figures in 10 rows of 10) did not result in a better understanding, while having a higher affective impact, and were perceived as larger compared to numerical formats [18,29].

Furthermore, the time horizon in which risks are presented is relevant. Time horizons may raise confusion, especially for long-term cumulative risks such as lifetime breast cancer risks [30]. Short-term risks such as risks for the next ten years may therefore be more meaningful and immediate [30], and may result in less overestimation. Research showed that for the presentation of breast cancer risks, women preferred risk information framed over multiple time horizons (10-year-, 20-year- and lifetime horizons) to risk information framed at one time point [31]. Until now, most studies used hypothetical scenarios in exploring patients' preference for the manner in which risk information is given. However, it is important to discover the best format for communicating cancer risk information in practice tailored to individual counsellees [26].

Several dimensions or outcomes in evaluating the effectiveness of the risk communication process have been distinguished [25,32,33]. Among these dimensions are, firstly, a cognitive evaluation, which refers to risk perception, and understanding and recalling the information provided. Acquisition of knowledge in the context of familial breast cancer comprises of understanding the nature of (familial) breast cancer, knowledge of personal risk factors, understanding the probability of developing breast cancer when having a genetic predisposition, and understanding what actions can be taken to reduce the risk. A second dimension is psychological well-being, including affective reactions and concern, for example, anxiety, (breast cancer) worries, and intrusive thoughts. A third dimension is the decision-making process including a behavioural evaluation, for example with regard to adherence to recommended behaviours (e.g. monthly breast self-examinations, mammography screening) and other decisions such as informing relatives who may be at risk. Finally, another dimension is how counsellees evaluate the information that is provided, which includes the extent to which the risk information is regarded as helpful and clear by counsellees.

Currently, protocols in genetic counselling for breast cancer contain no guidelines for the optimal format of risk communication. Therefore, counsellors present risks in ways that seem right to them despite a lack of evidence to support this [13]. Observational research shows that in breast cancer counselling, risks are given at least half of the time in verbal terms [34,35], and in 25% of the consultations in percentages [36].

In the Netherlands, current information booklets on hereditary breast cancer to support genetic counselling generally present risks, e.g. chance of developing breast cancer, as absolute percentages with a long-term time horizon ('lifetime risk'). In genetic counselling, generally the same formats are used, although one study recently revealed that a time horizon is not often stated in breast cancer counselling [35]. In addition, age-related risks regarding breast cancer counselling are usually not communicated, although in other countries, such as the UK, age-related risks are more commonly used [19].

### Objectives and research questions

The main objective of the present study is to evaluate the effects of different formats of risk communication on the counsellee's understanding and perception of the risk (cognitive outcomes), psychological well-being, and decision-making. In particular, we aim to investigate numerical versus graphical risk formats and lifetime breast cancer risks versus age-related risks. The research questions are:

1) What is the effect of the addition of a graphical format to standard risk information on cognitive outcomes, psychological well-being, and decision-making?

2) What is the effect of the addition of an age-related format to standard risk information on cognitive outcomes, psychological well-being, and decision-making?

3) What is the effect of the combination of both the addition of a graphical format and the addition of an age-related format on outcomes compared to research questions 1 and 2 (i.e. effect modification/interaction)?

4) How do the counsellee's personal experiences and characteristics mediate the effect on the communication of risk?

This article describes and discusses both the design and the content of the intervention of the BRISC (Breast cancer RISk Communication) study, a multicentre controlled clinical trial, to optimise the communication of breast cancer risks in genetic counselling among women with a family history of breast cancer.

## Methods and design

### Study design

The BRISC study is designed as a pre-post-test controlled group intervention trial with repeated measures using questionnaires. The trial is carried out in three of the nine familial cancer clinics in the Netherlands. The Medical Ethics Committees of the VU University Medical Center Amsterdam, the University Medical Center Groningen, and the Leiden University Medical Center approved the protocol in 2005.

### Intervention

The intervention consists of one additional consultation by a trained "risk counsellor" immediately after a standard genetic counselling session with a clinical geneticist, a clinical geneticist in training, or non-medical genetic counsellor, henceforth defined as a "genetic counsellor" (Figure 1). Since genetic counselling is seen as a psycho-educational endeavour with both educational and therapeutic elements [37], it is considered unethical to ask the genetic counsellors to present the intervention in a standardized and as objective a way as possible, thereby ignoring the specific needs of the patient. In addition, we assume that besides being unethical, it will not be feasible due to an additional workload for genetic counsellors.

**Figure 1 F1:**
[figure not shown]
Time planning of the intervention and questionnaires in the intervention group (conditions 1–5) and control group (condition 6).

During the additional consultation, risks are communicated in one of five ways (conditions), namely:

1) lifetime breast cancer risk in numerical format (in natural frequencies, i.e. X out of 100),

2) lifetime breast cancer risk in both numerical format and graphical format (i.e. population figures in 10 rows of 10),

3) lifetime breast cancer risk and age-related breast cancer risk in numerical format,

4) lifetime breast cancer risk and age-related breast cancer risk in both numerical format and graphical format, and

5) lifetime breast cancer risk in percentages.

Since the information given during the intervention not only differs from usual care regarding the format of the risks but also to the extent to which the information is structured, two control conditions are included. Condition 5, in which the risk is communicated in percentages as in the standard genetic counselling session (usual care), controls for the effect of giving risk information also in a structured way, enabling us to compare the effects of different risk formats. Condition 6, in which no intervention is given (usual care, henceforth defined as the control group) is used to control for the effect of repetition of the risk information (as compared to condition 5), and will control for Hawthorne effects [38].

As is shown in Table 1, the intervention includes information about risks of developing breast cancer, and having a hereditary predisposition for breast cancer. This includes: risk for an "average" woman in the Netherlands (population risk), risk for women with a *BRCA1/2 *mutation (carriers), and risk for women with the same family history as the counsellee. An example of risk information given in condition 1 is: "On average, 10 out of every 100 women in the Netherlands will develop breast cancer during their lifetime". In conditions 3 and 4, not only the structure of a cumulative risk is explained, but also age-related risks are presented (Figure 2). These age-related risks are computed based on Jonker et al. [39] and comprise breast cancer risks for the next ten years. An example of condition 3 is "In the current situation, on average 2 out of 100 women in the Netherlands of the same age as you (40), will develop breast cancer in the next ten years". In condition 2 and 4 risks are also presented as graphical display (see for example Figure 3).

**Table 1 T1:** Overview of risk information communicated in the intervention

**Population risk:**
Lifetime breast cancer risk: 10 out of 100 for breast cancer patients
Breast cancer risk due to hereditary causes: 5 to 10 out of 100
**Carriers of *****BRCA1/BRCA2***** mutation:**
Lifetime breast cancer risk: 60 to 80 out of 100
Risk passing a *BRCA1/BRCA2 *mutation to children: 50 out of 100
**Women with the same family history:**
Lifetime breast cancer risk:
- 11–20 out of 100 for women in a low risk category
- 20–30 out of 100 for women in a moderate risk category
- 30–40 out of 100 for women in a high risk category
Risk having a *BRCA1/BRCA2 *mutation: less than 10 out of 100 and specified if more than 10 out of 100

**Figure 2 F2:**
[figure not shown]
Risk communication formats in conditions 1–4.

**Figure 3 F3:**
[figure not shown]
**Example of graphical risk format used in condition 4**. "In the current situation, on average 2 out of 100 women in the Netherlands of the same age as you (40), will develop breast cancer in the next ten years"

### Usual care

In line with the guidelines of the Dutch Society of Clinical Genetics, genetic counselling generally includes information on the counsellee's lifetime breast cancer risk compared with the lifetime population risk [40]. Based on the individual lifetime risk, three breast cancer risk groups are distinguished: low (11–20%), moderate (20–30%), and high (30–40%). These estimates are mostly calculated using the Claus tables and modified Claus method, and primarily based on a woman's age and family history, including the number of first-degree- or second-degree relatives with breast cancer and the ages of onset of breast cancer [41].

Based on these guidelines, consensus is reached for the study to standardize the content and structure of the standard genetic counselling sessions (usual care) by presenting the woman's breast cancer risk as one of three risk groups, and using percentages for presenting risks. A "counselling checklist" is designed to be used as a guideline during the counselling session. The standard counselling procedures will be discussed with all counsellors involved.

### Study population

Women with a family history of breast cancer who are first-time attendees applying for breast cancer counselling are invited to participate in the study. A family history of breast cancer is defined as having or having had at least one first-degree- and/or paternal second-degree family member with breast cancer. Women are considered ineligible if they are under 18 years of age, have evident psychiatric illness or terminal disease, and are unable to read and write Dutch. Women with a personal history of breast or ovarian cancer are also excluded, because of the complexities in risk counselling of women with a previous history of cancer. Participants are allocated into an intervention or control group (for randomisation procedure, see below). Stratification to first-degree family members is applied to ensure that all family members receive the same condition.

### Sample size and power

The study will be powered on the main outcome measure, namely (change in) risk perception. In order to be able to detect a clinically relevant difference of 10–20% difference between the intervention group and the control group, a sample of 60 women per condition is needed (total n = 360). These calculations are based on a power of 0.80 (1-β) and a significance level of 0.05 (a; two-sided). With an expected drop-out rate of 20%, the sample size for the study is therefore determined at 450. Recruitment and data collection (including follow-up) is anticipated to continue for 31 months.

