### Randomisation

Randomisation takes place at 'condition round' level. The inclusion period is divided into condition rounds using a Latin Square design. Every round takes 5 months and switches when a total of n = 75 is reached. The ranking order of conditions (1–5) is varied to correct for learning effect by the risk counsellors. Each condition is given according to the design shown in Table 2. The control group (condition 6) is constructed in addition to each condition round.

**Table 2 T2:** Latin square design of condition rounds over time at the three clinical genetic centres

	**Conditions**^a^				
	months 1–5	months 6–10	months 11–15	months 16–20	months 21–25

Centre A	1	2	3	4	5
Centre B	2	3	4	5	1
Centre C	5	1	2	3	4

^a^. 1) lifetime risk in numerical format (natural frequencies); 2) lifetime risk in both numerical format and graphical format (population figures); 3) lifetime risk and age-related risk in numerical format; 4) lifetime risk and age-related risk in both numerical format and graphical format; 5) lifetime risk in percentages. Condition 6 (control group) is constructed in addition to each condition round.

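### The 60-per-condition calculation gives a two-fold effect range with no scale or SD, so it cannot be reproduced, and it shows no allowance for cluster allocation

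*Protocol article*

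**What the plan says.** Under Sample size and power, the article names the outcome: "The study will be powered on the main outcome measure, namely (change in) risk perception". The target effect and the number stand together in one sentence: "a clinically relevant difference of 10–20% difference between the intervention group and the control group, a sample of 60 women per condition is needed", which makes 360 over the six conditions. On the inputs it says "These calculations are based on a power of 0.80 (1-β) and a significance level of 0.05 (a; two-sided"). The only later step is "With an expected drop-out rate of 20%, the sample size for the study is therefore determined at 450". The paragraph gives no measurement scale, SD or intracluster correlation.

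Under Randomisation the article says "Randomisation takes place at 'condition round' level". Table 2 gives each of conditions 1–5 one five-month round in each of three centres, so three centre-rounds per condition. A round switches when 75 women are reached, and condition 6 is built up alongside every round. The Discussion calls the allocation cluster randomisation. Study population adds that first-degree relatives are kept in the same condition, and Procedure that each centre has one risk counsellor.

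Research questions 1–3 (Objectives) ask about adding a graphical format, adding an age-related format, and combining the two. These are comparisons between formats, whereas the power statement concerns intervention versus control.

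**The concern.** There are two separate problems.

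First, at fixed power and significance level, halving the effect quadruples the sample size. A range of 10–20% attached to a single n leaves the reader unable to tell which effect the trial was sized for. A null result could be read as ruling out a 10% difference that the trial may have had little chance of detecting.

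Second, women in the same centre-round share a counsellor, a centre and a period. If their answers are positively correlated, 60 women in three centre-rounds carry less information than 60 independent women. The paragraph goes from 60 to 360 to 450 without a step for this, so the 0.80 reads as the power of an individually randomised comparison, which this design is not.

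**Working it through.** **1. The plan's own totals.** 6 × 60 = 360, and 360 / (1 − 0.20) = 450. Both reproduce. The 20% dropout accounts for the whole of the inflation.

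**2. What 60 per condition detects if women are independent.** Two means, 1:1, two-sided 5%, power 80%: d ≈ (1.960 + 0.842) × √(2/60) = 0.511 by the normal approximation, and 0.516 by the t distribution. Call it 0.52 SD.

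**3. What SD this implies on a 0–100 scale.** The article gives none, so it is solved for (SD = difference / 0.516):

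| Difference for which 60 gives 80% | Implied SD | Consequence at the other end |
|---|---|---|
| 10 points | 19.4 | power for 20 points above 99%; about 16 per group would do |
| 20 points | about 39 | power for 10 points about 29%; about 4 × 60 = 240 per group needed |

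At intermediate SDs, power for 10 points is 77.5% (SD 20), 58% (SD 25) and 44% (SD 30). Sixty can give at least 80% over the whole range if the SD is 19.4 or less, but it is then the required number for 10 points only.

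**4. Cluster size.** Reading 75 as the total over the three centres, 5 × 75 = 375 women in conditions 1–5 plus 75 in condition 6 gives 450. Read as per centre, 15 × 75 = 1,125 would overshoot 450, so the first reading is used. Each centre-round then has 75 / 3 = 25 enrolled and 25 × 0.8 = 20 evaluable women.

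**5. Clustering, comparison of two formats.** Design effect = 1 + (20 − 1) × ICC; effective n = 60 / design effect; power is taken at 0.516 SD from the two-sample t distribution. The ICC values are assumptions. The detectable difference is the one with 80% power at the effective n.

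| Assumed ICC | Design effect | Effective n per condition | Power at 0.52 SD | Detectable at 80% |
|---|---|---|---|---|
| 0 | 1.00 | 60 | 80% | 0.52 SD |
| 0.01 | 1.19 | 50.4 | 73% | 0.56 SD |
| 0.02 | 1.38 | 43.5 | 66% | 0.61 SD |
| 0.05 | 1.95 | 30.8 | 51% | 0.73 SD |

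**6. Clustering, one format against condition 6.** If the 60 evaluable controls are spread evenly over 15 centre-rounds, each holds 60 / 15 = 4. Their design effect is 1 + 3 × ICC = 1.03, 1.06 and 1.15, giving effective n of 58.3, 56.6 and 52.2. Combined with the intervention side in step 5, power at 0.52 SD is about 76%, 72% and 61%. This ignores any round effect that controls and intervention women share, which would reduce the loss further.

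**7. The research questions, before clustering.** Conditions 1–4 form a 2 × 2 layout. A main effect compares 120 with 120: 2.802 × √(2/120) = 0.36 SD. The interaction is a difference of differences over four groups of 60: 2.802 × √(4/60) = 0.72 SD, or 0.73 SD by the t distribution.

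**The case against.** A reader might infer that 60 per condition does not give 80% power and that the stated power is simply wrong. The document does not support this. With no SD or scale, 60 is compatible with at least 80% power across 10–20 points whenever the SD is 19.4 or less. The outcome may also be a change or baseline-adjusted score with a smaller SD than the raw one. For example, an assumed raw SD of 25 with a pre-post correlation of 0.65 leaves 25 × √(1 − 0.65²) = 19.0, and power for 10 points is then about 82%. A condensed article may also leave the SD to the full protocol.

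Two lines of argument for the stronger claim also fail. Treating 10–20% as a difference in proportions produces low power figures, but no binary primary outcome is defined; risk perception is measured by numerical, rating and graphical scales. A cell-level test of three centre-rounds against three, with 4 degrees of freedom, gives still lower power. Most of that is a small-sample penalty, since it is only about 56% even at an ICC of 0, and it does not describe the powered contrast with condition 6, which runs alongside every round.

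On clustering, the ICC is unknown. Adjusting for centre and period could remove some between-round variation, though it also costs degrees of freedom. It cannot be strictly excluded that 60 already contains an allowance, but the text names only power and significance level as its basis. Finally, powering on one main contrast is a design choice, and the factorial main effects are in fact better served than the pairwise comparison; only the interaction is worse off.

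These points limit the size of the finding. They do not supply the missing scale, turn a two-fold range into one target, or show a clustering step.

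**Conclusion.** The point holds as a defect in the power statement, not as a demonstration that the trial is too small. Sixty per condition corresponds to one standardised difference, 0.52 SD, and cannot be the number required at both 10% and 20%. Which of the two it serves depends on an SD the article does not give.

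Separately, allocation is by condition round and no allowance for that is shown. Any positive ICC left after adjustment puts power below that of an independent-sample calculation. For ICC 0.01–0.05 the range is about 73% down to 51% between formats, and about 76% down to 61% against condition 6. These figures rest on assumed ICCs, about 20 evaluable women per centre-round, an even spread of controls, no centre or period adjustment, and 80% power before clustering. They show the possible size of the loss and do not estimate it. Keeping relatives in one condition adds a further correlation that is not quantified here.

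**What to change.** Leave the recruitment target of 450 unchanged and rewrite the paragraph so that it states what this number delivers:

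- Replace the 10–20% range with one difference on one named risk-perception scale, and give the SD used (raw, change or baseline-adjusted) with its source.
- State that 60 evaluable women per condition give 80% power for a pairwise difference of 0.52 SD before clustering.
- Add that, for comparisons between formats, the detectable difference becomes about 0.56–0.73 SD for an ICC of 0.01–0.05 with 20 evaluable women per centre-round. Label the ICC and cluster size as assumed, and say that the loss is smaller against condition 6 and depends on centre and period adjustment.
- Add the detectable effects for the research questions before clustering: 0.36 SD for the graphical and age-related main effects, and about 0.73 SD for their interaction.

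The cost is one rewritten paragraph and a less favourable stated detectable difference. No extra women are needed.
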